# Internet-delivered cognitive behavioral therapy for tinnitus compared to Internet-delivered mindfulness for tinnitus: a study protocol of a randomized controlled trial

**DOI:** 10.1186/s13063-023-07299-9

**Published:** 2023-04-12

**Keywords:** Internet-delivered interventions, Tinnitus, Cognitive behavioral therapy, CBT, ICBT, Mindfulness, MBTSR, iMBTSR, RCT, Tinnitus distress

## Abstract

**Background:**

Tinnitus affects around 15% of the population and can be a debilitating condition for a sizeable part of them. However, effective evidence-based treatments are scarce. One recommended treatment for tinnitus is cognitive behavioral therapy which has been found to be effective when delivered online. However, more treatments including mindfulness-based interventions have been studied recently in an attempt to facilitate the availability of effective treatments. There are promising findings showing great effects in reducing tinnitus-induced distress and some evidence about the efficacy of such intervention delivered online. However, there is a lack of evidence on how these two treatments compare against one another. Therefore, the aim of this study will be to compare Internet-delivered cognitive behavioral therapy for tinnitus against an Internet-delivered mindfulness-based tinnitus stress reduction intervention in a three-armed randomized controlled trial with a waiting list control condition.

**Methods:**

This study will be a randomized controlled trial seeking to recruit Lithuanian-speaking individuals suffering from chronic tinnitus. The self-report measure Tinnitus Handicap Inventory will be used. Self-referred participants will be randomized into one of three study arms: Internet-delivered cognitive behavioral therapy, Internet-delivered mindfulness-based tinnitus stress reduction intervention, or a waiting-list control group. Post-treatment measures will be taken at the end of the 8-week-long intervention (or waiting). Long-term efficacy will be measured 3 and 12 months post-treatment.

**Discussion:**

Internet-delivered interventions offer a range of benefits for delivering evidence-based treatments. This is the first randomized controlled trial to directly compare Internet-delivered CBT and MBTSR for tinnitus in a non-inferiority trial.

**Trial registration:**

ClinicalTrials.gov NCT05705323. Registered on January 30, 2023.

## Administrative information

Note: The numbers in curly brackets in this protocol refer to the SPIRIT checklist item numbers. The order of the items has been modified to group similar items (see http://www.equator-network.org/reporting-guidelines/spirit-2013-statement-defining-standard-protocol-items-for-clinical-trials/).

**Table Taba:** 

Title {1}	Internet-delivered cognitive behavioral therapy for tinnitus compared to Internet-delivered mindfulness for tinnitus: a study protocol of a randomized controlled trial
Trial registration {2a and 2b}.	This study has been registered in clinicaltrials.gov. ClinicalTrials.gov Identifier: NCT05705323 https://beta.clinicaltrials.gov/study/NCT05705323
Protocol version {3}	Protocol version 1.0, 2022–11-13
Funding {4}	This project has received funding from the Research Council of Lithuania (LMTLT), agreement No S-PD-22–178.

## Introduction

### Background and rationale {6a}

Tinnitus is the perception of an auditory sensation, perceivable without the presence of an external sound. The prevalence of tinnitus varies widely around the world, but it is estimated to affect approximately 10–15% of the population [1]. A recent pan-European study found that the prevalence of tinnitus was 14.7% and bothersome tinnitus 6% [2]. The same study also found that the occurrence of tinnitus becomes more prevalent as age increases and hearing deteriorates. There is still limited knowledge of the causal risk factors of tinnitus; however, there is some evidence for hearing loss and other physical conditions as well as depression being risk factors [3]. Additionally, the severity of tinnitus symptoms directly affects the utilization of healthcare resources for tinnitus management. The severity of tinnitus can be influenced by factors such as tinnitus awareness throughout the day, hearing loss, self-reported depression or anxiety, perceived loudness, education level, presence of additional physical symptoms, and variability in pitch and loudness [4, 5]. Some specific maladaptive psychological coping like avoidance and non-acceptance and negative cognitions about tinnitus has been suggested to be possible mechanisms of increased suffering from bothersome tinnitus [6–9]. Untreated bothersome tinnitus can significantly reduce the quality of life and may affect many other daily life aspects like sleep, concentration, and mental health [10]. Fortunately, psychological interventions can be effective in dealing with tinnitus-related disturbances.

### Cognitive behavioral therapy for tinnitus

Studies have found that cognitive behavioral therapy (CBT) is the most effective psychosocial treatment for tinnitus [11, 12]. Despite its established efficacy, CBT is very rarely offered to those experiencing distressing tinnitus [13]. CBT for tinnitus focuses on mechanisms thought to be behind the increased stressful reaction to tinnitus and disruption of habituation of tinnitus—negative interpretation of tinnitus, increased sympathetic arousal, selective attention and monitoring of tinnitus, and avoidance of tinnitus [13, 14]. Therefore, CBT for tinnitus usually includes elements aimed to alter these processes like psychoeducation and cognitive restructuring of negative beliefs about tinnitus, applied relaxation, and behavioral change, especially exposure to tinnitus as well as emotional reactions in response to tinnitus [13, 15, 16]. CBT focuses on cognitive and behavioral responses to tinnitus and aims to minimize distress caused by tinnitus rather than the symptom of tinnitus itself.

Practitioners treating patients with bothersome tinnitus are increasingly seeking new ways to increase access to cognitive behavioral therapy (CBT) due to its efficacy and success in treating tinnitus [17]. The creation of an Internet-based CBT intervention for tinnitus (ICBT) [15] is one such strategy, including the treatment components of face-to-face CBT but in a text form online and has additional features like illustrations and videos; it usually lasts 9 weeks, introduces new modules covering different topics weekly, and is often being supported by a clinician who answers questions and provides feedback on homework assignments during the whole treatment process [15]. ICBT has been found to be as effective for tinnitus as face-to-face CBT [18]. One study compared Internet-based cognitive behavioral therapy to individualized face-to-face clinical treatment in reducing distress from tinnitus, and the results showed that both interventions were equally effective in reducing tinnitus distress and the majority of tinnitus-related difficulties [19]. ICBT has also been found to be similarly effective as group CBT for tinnitus [20]. Systematic review and meta-analysis in 2019 reported results of nine randomized clinical trials (RCTs) in Europe that revealed positive outcomes and showed that ICBT was effective for adults, with improvements in anxiety, depression, quality of life, insomnia, and tinnitus distress [21]. Therefore, ICBT seems to be an effective and accessible way to provide help to people suffering from bothersome tinnitus.

Due to the fact that cognitive behavioral therapy is an effective treatment tool for helping people with tinnitus, there are also some limitations that are often discussed by researchers in such studies. The main challenge is finding a sufficient number of volunteers experiencing bothersome tinnitus. Having potentially come a long way before being able to seek audiology and otolaryngology services, some patients may wish to continue down this path and not to participate in a research study. Therefore, researchers will need to find more efficient recruitment strategies [19].

### Efficacy of mindfulness-based practice in the treatment of tinnitus

In the last decade, interest in mindfulness-based approaches as a potential management tool for tinnitus started to grow. As research on mindfulness-based interventions’ efficacy on various physical conditions, particularly chronic pain [22, 23] showed some promising results, new research incorporating mindfulness practices for tinnitus management started to come out. Kabat-Zinn in 1982 described mindfulness as a practice in the non-judgmental observation of all physical and mental events—body sensations, thoughts, and memories [24]. When explaining the potential benefit of mindfulness in the case of chronic pain, he details how through continuous practice a person develops an ability to observe without attachment an intense feeling in the body as a bare sensation, accompanying alarming thoughts—as simple mind events and this way decreasing the body’s alarm reactivity to body sensations [24]. The same benefits of practicing mindfulness can be experienced in the case of other physical and mental conditions, including tinnitus. Gans et al. describe mindfulness practice as helping those with tinnitus to notice thoughts, emotions, and body sensations as temporary events, rather than unbearable or unending sensations, therefore alleviating some of the co-occurring distress [25]. The most common and the most systematic training of mindfulness is done through mindfulness-based stress reduction (MBSR), Kabat-Zinn developed 8-week group program teaching techniques to practice non-judgmental awareness, mindfulness meditation, and acceptance of chronic conditions incorporating meditation, yoga, and psychoeducation [26]. However, teaching and promoting mindfulness practices have been incorporated into various modes of therapies and interventions, for example, mindfulness-based cognitive behavioral therapy has been developed [27].

Rademaker et al. did a systematic review of mindfulness-based interventions on tinnitus distress and found 7 studies testing some form of mindfulness-based intervention efficacy for tinnitus-related distress [28]. Previous studies were either testing mindfulness combined with cognitive therapy [29–31], interventions incorporating mindfulness as a core or additional element [32, 33], or MBSR program [25, 34]. Rademaker et al. [28] found that regardless of the type of mindfulness-based intervention reductions in tinnitus distress after the intervention was observed. However, these studies differ in specifics of their design and their findings, for example, how effective they were in secondary outcomes and whether effects were maintained at follow-ups. Rademaker et al. [28] reported that there was no effect of MBIs observed for depression and anxiety in tinnitus patients; however, this might be due to low scores of depression and anxiety of participants at pre-treatment.

It was hypothesized that mindfulness practice could help lessen judgment and reactivity to difficult body sensations and cognitions and therefore could be helpful in decreasing tinnitus distress [24, 25, 34]. Other studies of mindfulness-based interventions for tinnitus showed a more detailed view of possible mechanisms. McKenna et al.’s study results showed that after participating in mindfulness-based cognitive behavioral therapy, there were significant changes in tinnitus catastrophizing, avoidance behaviors, and tinnitus acceptance [31]. In Phillipot et al.’s study, at 3 months follow-up, the mindfulness group reported less negative emotion, irritability, and rumination than they reported before mindfulness training but already after psychoeducation session [30]. Gans et al. found improvements in participants’ mindfulness dimensions of non-judging, increase in observing, and in reactivity to inner experience [26]. Participants reported changes in how they accepted their bodies and their tinnitus experience in the qualitative part of the study [25]. The MBTSR course is designed to reduce participant’s anxiety about having tinnitus and provide accurate up-to-date education on tinnitus, while supporting a mindfulness meditation practice to relieve stress [26]. As explained by Rademaker et al. [28], these findings are in line with some cognitive conceptualizations of factors associated with bothersome tinnitus—negative cognitions, conditioned fear reaction to tinnitus, and tinnitus avoidance. Mindfulness-based interventions in helping to accept the experience of tinnitus, increasing cognitive and metacognitive awareness, and therefore decreasing negative thoughts and their effects should lower tinnitus distress [28].

However, many of the previously described studies combined mindfulness and cognitive behavioral techniques [29–31]; therefore, it is hard to exactly pinpoint the efficacy and exact mechanisms working in mindfulness versus cognitive techniques. Studies of mindfulness programs found significant reductions in the severity of tinnitus bother [25, 34], and Roland et al.’s [34] study found differences in functional connectivity within regions associated with known attention networks pre- and post-MBSR program. However, both studies were conducted without control groups and with small samples. While in Roland et al.’s [34] study participants attended a general MBSR course, Gans et al. [25] developed mindfulness-based tinnitus stress reduction (MBTSR) designed to address participants’ unique experience with tinnitus. The biggest modifications of MBSR were psychoeducation about tinnitus and psychoeducation related to the often co-occurring disorders common in people with tinnitus and guided mindfulness practices included more emphasis on awareness of sound and tinnitus perception [25]. MBTSR was recently implemented online, mirroring the in-person MBTSR program, and significant reductions in perceived stress and tinnitus self-function were found among those who finished the program [26]. This study by Gans et al. [26] investigated if there is a meaningful change in tinnitus intrusiveness after taking the Internet-delivered iMBTSR course and whether changes were retained at a 6-month follow-up. The results showed a significant reduction in tinnitus intrusiveness with the greatest gains noted between pre-treatment to mid-treatment. Gains were maintained 6 months after treatment demonstrating the efficacy of this Internet-delivered 8-week course [26].

### Internet-based mindfulness and cognitive behavioral therapy for tinnitus

While there is enough evidence for the efficacy of cognitive behavioral therapy for tinnitus and emerging evidence of mindfulness as an effective tool for managing tinnitus, previous research on mindfulness interventions for tinnitus were studying mindfulness combined with cognitive behavioral therapy techniques or had no control group to compare the efficacy to. Finally, no previous study compared mindfulness-based intervention directly to cognitive behavioral therapy for tinnitus. Testing Internet-based versions of both interventions in comparison with the control group will be another step toward facilitating wider access and a range of effective psychological interventions for tinnitus distress.

### Objectives {7}

The purpose of this study is to assess the efficacy of Internet-delivered cognitive behavioral therapy (CBT) and Internet-delivered mindfulness-based tinnitus stress reduction intervention for adults with tinnitus, by comparing their efficacy against each other and against a waiting list control group.

### Trial design {8}

This study is three-armed parallel-group randomized controlled non-inferiority trial. Participants will be randomized to all groups equally.

## Methods: participants, interventions, and outcomes

### Study setting {9}

This study will be conducted completely remotely. All screening and outcome questionnaires will be completed online and intake, and post-treatment interviews will be done on the phone. The intervention is provided via a web-based platform and is mobile device friendly. All participants who speak Lithuanian regardless of their place of residence will be considered for participation in the trial as long as they are available for an interview over the phone. The participant flowchart is shown in Fig. 1.

**Fig. 1 Fig1:**
[figure not shown]
CONSORT diagram

### Eligibility criteria {10}

All participants will have to complete self-report online questionnaires, and participants meeting all the main inclusion criteria will undergo additional intake interviews over the phone. Participants will be deemed eligible to participate in the study if they meet the following inclusion criteria: (1) 18 years and older, (2) experience tinnitus for at least 3 months, (3) scores 28 or more on Tinnitus Handicap Inventory, (4) has the ability to use a computer (or smartphone or tablet) with a connection to the internet for the duration of the study, and (5) comprehension and ability to write and speak in the Lithuanian language. Participants will be excluded from the study if they meet one of the exclusion criteria: (1) inability to allocate sufficient time for participation in an 8-week intervention, (2) significant medical or psychiatric conditions which would prevent participation, and (3) participation in other tinnitus interventions during the study.

### Who will take informed consent? {26a}

Participants will give their informed consent online by indicating a checkbox before starting to complete self-report questionnaires.

### Additional consent provisions for collection and use of participant data and biological specimens {26b}

N/A, no biological specimens will be collected.

### Interventions

#### Explanation for the choice of comparators {6b}

Internet-delivered cognitive behavioral therapy for tinnitus has accumulated a sizeable amount of evidence of its efficacy. Recent studies reported that mindfulness-based stress reduction interventions could also be effective in alleviating tinnitus-related distress. A waiting-list control will allow to compare how this particular intervention compares to those provided in previous studies.

#### Intervention description {11a}

Participants will be randomized to either of the two treatment groups or a waiting-list control group. After waiting for 8 weeks, participants in the waiting-list control group will have to choose one of the two interventions.

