#### Primary outcome measures

To assess the impact of tinnitus on daily life, the Tinnitus Handicap Inventory (THI) will be used [37]. Assessment with THI will take place at pre-treatment, post-treatment at week 8, and 3 and 12 months post-treatment follow-ups. Change in the score from baseline will be assessed. The THI is designed to assess the impact of tinnitus on daily life and measures tinnitus-related functional limitations and emotional and catastrophic reactions. It is also widely used in research studies to measure the change in the severity of a tinnitus handicap before and after an intervention and therefore was selected as the primary measure of the study. The THI questionnaire consists of 25 questions. Answers are scored as follows: “yes,” 4 points; “no,” 0 points; and “sometimes,” 2 points. The total score is obtained by summing the scores of all 25 questions. A higher score indicates a higher disability caused by tinnitus and a higher impact of tinnitus on a person’s daily life. A validated Lithuanian language version of THI will be used in the study [38].

Weekly monitoring of changes in tinnitus handicap severity will be done using the Tinnitus Handicap Inventory Screening version (THI-S) [39]. A screening version of THI has 10 items from the original THI and will let assess the changes throughout the duration of the program. Assessment with THI-S will be done at weeks 2, 4, and 6.

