### Data collection and management

#### Plans for assessment and collection of outcomes {18a}

Data will be collected at pre-randomization, termination, and 3- and 12-month follow-ups. All questionnaires will be self-report and administered online. To ensure that collected data is complete and accurate, the online questionnaires will be coded in a way that requires participants to fully answer the questions in order to submit the answers. For a full timeline of questionnaire dissemination, see Table 1.

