## Statistical methods

### Statistical methods for primary and secondary outcomes {20a}

The differences between the groups at baseline will be evaluated using independent samples *t*-tests for continuous variables and chi-square tests for categorical variables or their non-parametrical equivalents. In order to assess the potential changes in the primary and secondary outcomes and compare them between the intervention groups and the control group, repeated-measures ANOVAs will be performed. The results from all baseline assessment measures will be utilized as predictors. The study will calculate both within-group and between-group effect sizes. The between-group effect sizes will be determined by calculating the mean difference from the pre-test to the post-test for short-term effects and from the pre-test to follow-up for long-term effects, using the standard deviations of each group at the pre-test. The within-group effect sizes will be calculated using the means and standard deviations at all time points for every group. We will use regression analysis to investigate the association between baseline variables and outcome measures, with the goal of identifying predictors of the outcome.

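### Comparisons with the waiting list are not limited to week 8, although that whole arm moves to a self-chosen active programme at that point

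*Protocol article*

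**What the plan says.** - **Crossover.** Intervention description {11a}: "After waiting for 8 weeks, participants in the waiting-list control group will have to choose one of the two interventions". This applies to the whole arm, and the programme is chosen, not randomised.
- **Visits.** Primary outcome measures, on the Tinnitus Handicap Inventory (THI): "Assessment with THI will take place at pre-treatment, post-treatment at week 8, and 3 and 12 months post-treatment follow-ups". The secondary measures PHQ-9, GAD-7, ISI, MAAS and TCQ follow the same schedule. Plans for assessment {18a} describes the trial as a whole: "Data will be collected at pre-randomization, termination, and 3- and 12-month follow-ups". Table 1 has no separate schedule for the waiting list.
- **Main analysis.** Statistical methods {20a} assesses changes in the primary and secondary outcomes, to "compare them between the intervention groups and the control group, repeated-measures ANOVAs will be performed". No time points are named.
- **Long-term effect sizes.** The same section defines between-group effect sizes from the mean difference between pre-test and post-test for the short term, and "from the pre-test to follow-up for long-term effects, using the standard deviations of each group at the pre-test". No arm is excluded.
- **Objective.** Objectives {7} sets out to assess both programmes "by comparing their efficacy against each other and against a waiting list control group", without naming a time point.
- **Non-inferiority endpoint.** Sample size {14} fixes this as THI at 8 weeks.

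**The concern.** The waiting list is an untreated randomised comparator only until week 8. After that, each of its members has been directed to one of the two programmes under study, according to preference. An analyst who follows {20a} literally would put all three arms and all visits into the ANOVA, and would compute a pre-test-to-follow-up effect size for each active arm against the waiting list.

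Those follow-up figures would not estimate treatment against no treatment. They would estimate immediate treatment by allocation against delayed treatment by choice, a quantity that the article does not define. If both programmes work and the effect lasts, the active arms and the former controls converge. A reader who sees a clear difference at week 8 and a small one at 12 months could conclude that the benefit had faded, when the controls had simply been treated.

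**Working it through.** No stated figure of the plan is at issue. The sample size of 42 relates to the week-8 endpoint and does not enter here. The check has three steps.

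**1. Is any untreated control left at follow-up?** Both programmes last 8 weeks. If controls start when the waiting period ends, they are treated from about week 8 to week 8 + 8 = 16. Counted from week 8, the follow-ups fall at about week 8 + 13 = 21 and week 8 + 52 = 60, both after controls could have completed a programme. If post-treatment is instead counted from the end of each control's own delayed programme, controls have by definition been treated before follow-up. Either reading gives the same answer: none is left.

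**2. What does the follow-up contrast estimate?** Let *d* be the standardised effect of an active arm against untreated controls, assumed to persist. Let *f* be the share of that effect that controls have gained by follow-up. Then

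contrast at follow-up = *d* × (1 − *f*)

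The article gives neither *d* nor *f*, so both are assumptions, shown over a range:

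| *f* | *d* = 0.5 | *d* = 0.8 |
|---|---|---|
| 0 (controls untreated) | 0.50 | 0.80 |
| 0.5 | 0.25 | 0.40 |
| 0.75 | 0.125 | 0.20 |
| 1 | 0 | 0 |

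On the THI scale, with an assumed 15-point effect, the contrast would be 15, 7.5, 3.75 and 0 points.

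**3. Does the ANOVA lose power?** Comparing change between groups in a repeated-measures ANOVA is the group-by-time interaction. Assume two groups of 14, four visits, SD 18, correlation 0.6 between visits, a 15-point effect that is held, and full catch-up by controls (*f* = 1). The group differences over the four visits are

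- with crossover (0, 15, 0, 0): mean 3.75, sum of squares about the mean 225 − 4 × 3.75² = 168.75
- without crossover (0, 15, 15, 15): mean 11.25, sum of squares about the mean 675 − 4 × 11.25² = 168.75

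The noncentrality is (14/2) × 168.75 / (18² × (1 − 0.6)) = 1181.25 / 129.6 = 9.11 in both cases, with power of about 0.69 in both. The test does not weaken in this scenario, but its meaning changes. With crossover, a significant interaction reflects a week-8 difference followed by convergence, so it cannot show a lasting advantage over control.

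**The case against.** **The text never says that the arms are compared with control at 3 and 12 months.** This is the strongest counter-argument, and it is literally true. The ANOVA sentence names the control group but no visits. The effect-size sentence names follow-up but not the control group, and it would fit a comparison of ICBT with iMBTSR, which is still as randomised. The abstract mentions waiting only for the post-treatment measurement. The CONSORT figure is not shown, and it or a separate analysis plan may restrict waiting-list follow-up. So the point is an inference from unrestricted wording. It still stands, because {20a} positively specifies both analyses, the schedule gives all arms the same visits, and no visible text narrows either analysis.

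**A reader might infer that long-term efficacy against control is a stated aim.** The article does not support that. Objectives {7} names the waiting list without a time point, and the abstract names long-term efficacy without naming control. Only joining the two gives such an aim.

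**A reader might infer a large loss of power.** In the scenario of step 3, power for the group main effect does fall, from about 48% to 10%. But that effect averages over all visits, including baseline, and is not the test of differential change that {20a} describes. The interaction has the same power with and without crossover, so no power-loss figure should be claimed.

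**The crossover is openly disclosed.** That makes misreading less likely, but it does not change what a follow-up contrast with this arm estimates.

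**Conclusion.** The point holds, within limits. As written, {20a} allows 3- and 12-month contrasts with an arm that has by then moved to active treatment of its own choosing. Such contrasts cannot be read as efficacy against no treatment. They would tend towards zero if the programmes work: half the effect remains if controls gain half of it, and none if they gain all of it. Those shares, and the persistence of benefit in the active arms, are assumptions; the absence of an untreated comparator is not.

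The problem is confined to follow-up contrasts that involve the waiting list. The week-8 non-inferiority test, the week-8 contrasts with the waiting list, and ICBT against iMBTSR at 3 and 12 months are unaffected. The documents do not support a claim that the trial's main comparison is compromised or that the ANOVA loses power.

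**What to change.** Amend Statistical methods {20a} before analysis so that:

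- every comparison with the waiting list, in the ANOVAs and in the between-group effect sizes, covers baseline to week 8 only;
- between-group comparisons at 3 and 12 months are ICBT against iMBTSR as randomised;
- waiting-list data after crossover are reported separately and descriptively, by chosen programme, and stay out of the follow-up levels of the model and out of the long-term between-group effect sizes.

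If the CONSORT figure or an analysis plan already says this, {20a} needs only a sentence that agrees with it.

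The change needs no further participants or visits. Its small cost is giving up a long-term controlled contrast that the design cannot support.
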